For veterans prescribed psychotropic medications (i.e., antidepressants, antipsychotics or anxiolytics/sedative-hypnotics), the veteran is required to be on a stable dose for at least five weeks prior to screening. For veterans not taking psychotropic medication, a minimum of five half-lives must elapse prior to screening since the veteran last took any given psychotropic medication. Should it be necessary to adjust a patient's treatment regimen during the 3 month treatment period, standard pharmacological care for PTSD will be instituted. Major depression and other anxiety disorders are not exclusionary since they frequently co-occur with PTSD and it remains unclear whether their presence represents true comorbidity, symptom overlap, or severe illness. Since mild head trauma is common in the military population in general, excluding such participants would diminish the generalizability of the sample; participants with severe traumatic brain injury (TBI), defined as an extended period of unconsciousness or amnesia following injury, will be excluded. The Ohio State University (OSU) TBI Identification Method will be used to assess lifetime history of TBI. This method first establishes all significant injuries in one's life and then determines if a TBI may have occurred based on whether the participant experienced a loss of consciousness (LOC) and, if so, for how long. A person is said to have a mild TBI if LOC does not exceed 30 minutes for any injury, a moderate TBI if LOC is between

30 minutes and 24 hours, and a severe TBI if LOC exceeds 24 hours. The OSU TBI assessment will be administered by a trained rater during the psychiatric evaluation conducted at screening.

Additionally, veterans diagnosed with alcohol/substance abuse and dependence will be excluded only if they are recently engaged in a maladaptive pattern of use or abuse. More specifically, persons who meet diagnostic criteria for alcohol/substance dependence will be excluded if they have manifested dependence within the previous three months (i.e., have met three or more of the seven criteria for a maladaptive pattern of use in the last three months). Persons with alcohol/substance abuse (who, by definition, do not meet criteria for alcohol dependence) will be excluded if they have shown a maladaptive pattern of alcohol use during the past one month (i.e., have met one or more of the four criteria for a maladaptive pattern of abuse).

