#### 4.a.1. Inclusion Criteria

1. Participant is a male veteran.
2. Veteran meets DSM-IV diagnostic criteria for chronic PTSD.
3. Veteran has a CAPS total score (past month symptom status) greater than or equal to 50 at screening.
4. For veterans taking psychotropic medications (i.e., antidepressants, antipsychotics or anxiolytics/sedative-hypnotics), the veteran will be on a stable dose for at least five weeks prior to screening.
5. For veterans not taking psychotropic medication, a minimum of five half-lives must elapse prior to screening since the veteran last took any given psychotropic medication.

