Concomitant medications will be recorded in terms of their daily dose, indication, and start and stop date. Study drug compliance will be monitored by pill counts of returned medication. In addition to the monitoring of individual patients at the local site, the study will be reviewed by the CSR&D Psychiatric, Behavioral Health & Neurologic Disorders Centralized Data Monitoring Committee.

Study participants will be monitored at each clinic visit (day 3, weeks 1, 4, and 12) and via telephone contact (weeks 2, 6, 8, and 10) by site investigators and coordinators for AEs and SAEs. Participants will be asked about any AEs or SAEs that have occurred since the previous visit or telephone contact, and vital signs will be obtained at all in-person visits. This frequent contact with participants, both in-person and via telephone, will enable site investigators to monitor safety, obtain PTSD symptom ratings, and identify any signs of deterioration. Information on all AEs and SAEs, including those related to the study intervention and those not related to the intervention, will be collected and recorded on the appropriate study event forms. All relevant information (e.g. onset of event, severity, outcome, extent to which it is or is not attributable to the drug or other study procedures) will be captured. Active monitoring of AEs and SAEs will begin as soon as a study participant signs the informed consent document and will continue through end-of-study for each participant. Instructions for contacting the VA National Suicide Hotline will be incorporated into the consent form and instructions for patients as part of safety monitoring. These safety data will be analyzed as described in the Analysis Plan (4.q.) and used to inform additional studies with mifepristone in the treatment of PTSD.

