- c. A continuous mixed-effects model for longitudinal observations of CAPS scores will also be used adjusting for aforementioned baseline characteristics, indicator variable that contrasts

mifepristone vs. placebo, and plasma levels of mifepristone and its metabolites at one week to determine the effect of them on CAPS scores trajectories.

Although it is not listed as an outcome, the percentage of unique participants with concurrent psychotropic medication use change by 1 month and by 3 month (end of the trial) will be compared between mifepristone and placebo using chi-square tests. Concurrent psychotropic medication change is defined as seeking a rescue medication for those who are not on concurrent psychotropic medication prior to randomization, or seek a new psychotropic medication or require a dose increase for those on a stabilized regimen treating PTSD prior to randomization. Those analyses will also be based on mITT principle. Except the primary analysis of the primary outcome, all efficacy and safety analyses will be performed with a significance level of 5% for two-sided tests. Due to exploratory nature of the study, and the sample size was not powered on hypothesis testing framework, careful consideration is necessary when interpreting the significance of these results on the primary, secondary and descriptive outcomes. The results of the trial are considered to be hypothesis generating and are not to obtain definitive efficacy information. No adjustments for multiplicity on various secondary outcome measures are planned in this phase IIa trial. The lack of adjustment will be noted in the resulting manuscripts.

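### Read literally, the definition of psychotropic medication change cannot count participants whose stable psychotropic is recorded for something other than PTSD

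*Protocol*

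**What the plan says.** The closing paragraph of Descriptive Outcomes in Protocol Section 4.p.1 adds one comparison outside the listed outcomes: "Although it is not listed as an outcome, the percentage of unique participants with concurrent psychotropic medication use change by 1 month and by 3" months, tested between arms by chi-square on the mITT set. It then defines the event in two branches.

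- Participants not medicated at randomization: a change is "defined as seeking a rescue medication for those who are not on concurrent psychotropic medication prior to randomization".
- Participants medicated at randomization: a change is to "seek a new psychotropic medication or require a dose increase for those on a stabilized regimen treating PTSD prior to randomization".

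Three other places decide whom this rule has to cover and what data are at hand.

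- Section 4.a.1, item 4: "For veterans taking psychotropic medications (i.e., antidepressants, antipsychotics or anxiolytics/sedative-hypnotics), the veteran will be on a stable dose" for a set period before screening. No indication is named.
- Section 4.a: "Major depression and other anxiety disorders are not exclusionary since they frequently co-occur with PTSD".
- Section 4.i: "Concomitant medications will be recorded in terms of their daily dose, indication, and start and stop date".

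**The concern.** The two branches look like a complete split into medicated and unmedicated participants, but the second carries an extra condition: the stable regimen must be one that treats PTSD. Entry carries no such condition, and the protocol expects co-morbid depression and anxiety. A participant on a stable antidepressant recorded for depression, or a stable hypnotic recorded for insomnia, is medicated and so outside the first branch. His regimen is not recorded as treating PTSD, so he is outside the second. If a new drug is added or his dose is raised in week 2, nothing in the rule lets it count.

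The event words add a smaller difficulty. *Seeking* and *seek* describe what the participant asks for, whereas the data to be analysed are recorded starts and doses.

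What is at stake is limited but real. Section 4.g discourages treatment adjustments, especially in the first month, because they may confound the primary endpoint. It also lets participants who have them stay in the study. This chi-square comparison is the only place in the protocol where psychotropic changes after randomization are set side by side by arm. A reader who wants to know whether co-medication differed between arms will look here.

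**Working it through.** **Step 1. Does the rule cover everyone admitted?**

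| Psychotropic at randomization | Admitted by Section 4.a.1? | Branch of the definition | Can a later start or increase count? |
|---|---|---|---|
| None | Yes, item 5 | First | A start, yes |
| Stable, recorded for PTSD | Yes, item 4 | Second | Yes |
| Stable, recorded for another indication | Yes, item 4 | Neither | No |

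The third row is the gap. These participants are still in the mITT set, which Section 4.p.1 defines by randomization and not by medication, so they stay in the denominator. Elsewhere in Section 4.p.1, psychotropic use is classified without regard to indication: in the baseline comparison, the subgroups of the primary outcome and the covariates of the mixed model. The PTSD condition in this one definition is the exception. Indication is a recorded field (Section 4.i), so a programmer could apply the condition as written.

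**Step 2. How large could the gap be?**

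The protocol gives no expected rate of medication change, so there is no figure to reproduce. The following is an illustration only. Inputs:

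- 45 per arm: Section 4.n.2.
- m, share medicated at entry: not given for this trial. Assumed 0.50 to 0.80. Section 1.a cites 50% and 80%, but for veterans starting PTSD treatment and veterans in chronic PTSD care, not for this sample.
- f, share of medicated participants whose regimen is recorded for another indication: not given. Assumed 0.10 to 0.50.
- r, true rate of starts or increases: not given. Assumed 0.20 in all participants.

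Uncountable share u = m × f. Participants affected per arm = 45 × u. Rate under the literal rule = r × (1 − u).

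| m | f | u | 45 × u | 0.20 × (1 − u) |
|---|---|---|---|---|
| 0.50 | 0.10 | 0.050 | 2.25 | 0.190 |
| 0.50 | 0.25 | 0.125 | 5.6 | 0.175 |
| 0.50 | 0.50 | 0.250 | 11.25 | 0.150 |
| 0.80 | 0.10 | 0.080 | 3.6 | 0.184 |
| 0.80 | 0.25 | 0.200 | 9.0 | 0.160 |
| 0.80 | 0.50 | 0.400 | 18.0 | 0.120 |

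So about 2 to 18 of 45 per arm could not be counted, and a true 20% would read as 19% to 12%. In people, 20% of 45 is 9 and the shortfall is 9 × u, from 9 × 0.05 = 0.45 to 9 × 0.40 = 3.6 per arm. With f = 0, u = 0 and nothing is lost.

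**Step 3. What happens to the comparison between arms?**

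If u is the same in both arms, and those left out change as often as the rest of their arm, both rates are multiplied by (1 − u). The difference between them is then multiplied by (1 − u) too: 0.95 to 0.60 of its true size over the range above. The comparison is pulled towards no difference. This gives no ground for saying that it is tilted towards one arm.

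**The case against.** The best defence is that *treating PTSD* is loose wording for any stable psychotropic. Sections 4.a and 4.a.1 sort entrants into two groups, stably medicated and unmedicated, and the feasibility text in the recruitment section does the same. The two branches mirror that split. Section 4.a also declines to separate co-occurring depression or anxiety from PTSD itself, and Section 1.a treats depression, anxiety and sleep disturbance as symptoms associated with PTSD. On that reading nobody is left out. This is plausible, and it is why the effect may be nil. It does not remove the fault, because the text does not say which reading applies and the recorded indication invites the literal one.

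The defence also notes that the measure is descriptive, that the trial is described as hypothesis generating, and that an SAP may turn the sentence into working rules. All of that limits the weight of the point. But this is a rule the protocol itself states, not one that it leaves open.

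Two stronger readings are tempting and do not stand.

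- A reader might infer that the rule counts requests instead of changes. *Seek* is poor wording, but requiring a dose increase is not a request, and the protocol describes no data field for requests that led to no prescription.
- A reader might infer that leaving out dose reductions and stops is a counting error. Section 4.g describes adjustment mainly as a response to deterioration, and the definition speaks of rescue, new drugs and increases. That is a coherent escalation measure. Only the label, medication use change, is broader than the content.

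**Conclusion.** The point holds as a defect of definition. The two branches do not cover every participant whom the entry criteria admit, and the event is worded as seeking where a recorded start is presumably meant. The likely consequence is an understated or blurred descriptive comparison.

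A reader might go further and conclude that the reported change rates will be wrong, or that the primary result is affected. The documents support neither. The size rests on m and f, which the protocol does not give. Over the assumed ranges it is 2 to 18 participants per arm who could not be counted, and it is nil if every stable regimen is taken to treat PTSD. The calculation assumes the same change rate in all participants and shows no loss that differs between arms; in a randomized, double-blind trial none is expected. The responder analysis does not use this definition. It is worth correcting because the correction is cheap and this is the only by-arm look at changes that Section 4.g itself regards as possible confounders.

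**What to change.** Replace the definition in the closing paragraph of Descriptive Outcomes (Section 4.p.1) with one event for all mITT participants: *any psychotropic (antidepressant, antipsychotic, anxiolytic/sedative-hypnotic) started, or any psychotropic dose increased, after randomization, whatever the indication and whatever the medication status at randomization, derived from the recorded start dates and daily doses*. Delete the condition *treating PTSD* and the words *seeking* and *seek*. Label the measure escalation/rescue, so that the name matches what is counted. A separate row by arm for dose reductions and stops is optional.

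The cost is one reworded sentence. The data needed are already collected under Section 4.i, the time points and the test stay as they are, and no clinical rule changes. The small downside is that some counted changes will have nothing to do with PTSD; the recorded indication can show which.

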#### 2.a.3. *Safety, tolerability and dosing*

The proposed study is grounded in the use of established clinical and experimental methods. In all previous studies of mifepristone in neuropsychiatric disorders, a pulse dose strategy has been employed with administration of mifepristone for 4-8 days. The majority of these studies used a dose of 600 mg/day (Belanoff et al., 2001; Belanoff et al., 2002; Young et al., 2004; Simpson et al., 2005; Gallagher et al., 2005; Flores et al., 2006; DeBattista et al., 2006; Blasey et al., 2009); 1200 mg/day has been studied in psychotic depression (Belanoff et al., 2002) and is being used in current studies of mifepristone in psychotic depression. In a recent Phase III trial of 600 mg/day of mifepristone in psychotic depression, a dose-response relationship between plasma concentration of mifepristone and treatment response was found. Only about one-third of the participants achieved what was previously determined to be the optimal blood level of mifepristone in depression. If a similar dose-response relationship exists in PTSD, some participants would need a higher dose of mifepristone to achieve clinical response; yet, in our pilot data there is preliminary evidence of a treatment effect at 600 mg/day. Accordingly, we will examine the effects of 600 mg/day of mifepristone and post-treatment mifepristone levels on clinical response. According to [name], rash is estimated to occur in 1% of persons treated with 300 mg/day of mifepristone, 3.3% of persons treated at 600 mg/day, and 5.5% of persons treated with 1200 mg/day (Corcept Therapeutics).

With respect to HPA axis activity, based on the results of the ACTH and CRF stimulation tests, pituitary and adrenal reserves are maintained during mifepristone treatment (Bertagna et al., 1994). Chronic treatment with mifepristone does not appear to be associated with the development of iatrogenic adrenal or pituitary insufficiency. Based on published reports and personal communication with [name] of Corcept Therapeutics, adrenal insufficiency has never been observed with one week of mifepristone treatment in depressed patients. (See also the section on monitoring adverse events, 4.i., for details on safety monitoring.) Nonetheless, since mifepristone is contraindicated in adrenal insufficiency, for safety reasons participants with a known history of this disorder or with low screening plasma cortisol levels will be excluded.

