In a study of 7-14 days of treatment with mifepristone (10 mg/kg/day) (Laue et al., 1990), no changes

were observed in multiple laboratory measures including complete blood cell count, erythrocyte sedimentation rate, C-reactive protein, antinuclear antibodies (ANA), rheumatoid factor, and multiple quantitative immunoglobulin measures. In multiple subsequent trials of mifepristone, the drug was not associated with significant side effects (Belanoff et al., 2001; Belanoff et al., 2002; Young et al., 2004; Simpson et al., 2005; DeBattista et al., 2006; Flores et al., 2006). In the largest of these trials, psychotically depressed individuals were treated with 600 mg/day of mifepristone (n=105) or placebo (n=116) for one week, followed by usual treatment; there were no significant differences in the incidence of rash or multiple other potential side effects including headache, nausea, vomiting, constipation, dizziness, insomnia, sedation, abdominal pain, or toothache (DeBattista et al., 2006).

Another issue concerns whether it is ethical and safe to enroll veterans in a placebo-controlled medication trial. We believe it is ethically justified in the present trial since FDA-approved pharmacological options for the treatment of PTSD have not been shown to be effective in veterans with PTSD (Hertzberg et al., 2000; Friedman et al., 2007), and since the IOM report concluded that there is no evidence of efficacy for commonly used pharmacotherapies in veterans with PTSD. For safety purposes, many safeguards have been put in place including the exclusion of patients at risk for suicide, frequent monitoring of suicidality and clinical state throughout the project, and the ability of the investigator to adjust medications or treatment plan if needed, without dropping the patient from the study, if his clinical condition deteriorates; these safeguards are described in detail elsewhere (see section 4.i. for details on safety monitoring). Numerous steps have been taken to ensure that patients will be safe and will receive standard pharmacotherapy if necessary. Overall, the proposed study is designed with a favorable risk to benefit ratio for male veterans with PTSD.

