Common Terminology Criteria for Adverse Events (CTCAE) and Common Toxicity Criteria (CTC). Common events known to be associated with mifepristone will be assessed using the reference toxicity table included in the study manual of operations to decrease the variability across investigative sites. Per the FDA's request, the investigators will explicitly inquire about the development of a rash since this is a known side effect of mifepristone. Medication will be discontinued if a rash develops or adrenal insufficiency is suspected; for the latter, a referral to internal medicine and/or endocrinology will be made. If the rash is severe or persistent, the veteran should be referred to a dermatologist.

With respect to suicidality, veterans with a history of attempted suicide within the previous two years or active suicidal ideation within the past month (participant endorses active suicidal ideation with any methods without intention to act (question 3)), as assessed by the C-SSRS, will be excluded. For all study participants, suicidality will be re-assessed at in-person post-treatment visits (one week follow-up, one month follow-up, and three month follow-up) using the C-SSRS. If the participant develops active suicidal ideation (as elicited from the C-SSRS or spontaneously reported) at any point in the study, he will be further assessed; the appropriate clinical intervention will be initiated and the local procedures for notifying the suicide prevention coordinator will be followed.

To assist in monitoring patient safety, the sites will be provided with an Investigational Brochure (IB) prepared by Corcept Therapeutics and a Drug Information Report (DIR) that is prepared and updated as needed by the pharmacy coordinating center study clinical pharmacist. The DIR provides a comprehensive review of the published literature regarding mifepristone safety data as used in the treatment of psychiatric disorders. The IB and DIR are submitted along with the protocol to the IRB, the DMC, and to the FDA as part of the IND as the safety information for the study. The statistical coordinating center then distributes the IB, DIR, protocol, and Drug Treatment and Handling Procedure manual to the study sites.

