##### 4.n.2. *Sample size determination*

As mentioned above, the sample size has been calculated to provide at least 90% probability that mifepristone 600 mg has been correctly identified as being superior to placebo if the population difference in response rate is at least 15%. Using the calculations provided by Simon et al. (1985) and accounting for a 20% attrition rate which has been reported in other drug studies using a similar population (Bartzokis et al., 2005), a total sample size of 90 is required, or 45 per treatment group. Since the sample size varies according to the responder rate (as well as the magnitude of the difference of interest), and the responder rate for placebo is unknown, we assume a placebo responder rate of 40%, which is at the high end of the studies referenced above. By contrast, in order to have a one-sided Type I error rate of 5% and 80% power to detect the 15% difference between two

groups using a traditional hypothesis testing framework, the study would require 274~344 participants when the placebo responder rate changes from 20% to 44%, after adjustment for a 20% withdrawal rate. If the true population difference in response rate is smaller than 15% (between 10~12%) and if we still consider it clinical significant, the proposed sample size (n=72 completers or 90 with 20% withdrawal rate) will still provide at least 80~85% probability of correctly identifying the superior group.

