#### Secondary Outcomes:

1. The analysis specified for the one-month responder rate will also be done for the three-month responder rate as a secondary analysis to check for the sustainability of the response.

Additionally, a continuous mixed-effects model for longitudinal observations of CAPS (past week symptom status) scores (week 1, 4 and 12) will be used. Covariates including baseline characteristics, specifically duration of symptoms, duration of illness since trauma, concurrent psychotropic medication use prior to randomization, overall extent of the psychiatric co-morbidity, military cohort, and site will be explored in the adjusted analysis. This analysis will provide a treatment effect in terms of the slope of the interaction term between group and time variables, conditional on aforementioned covariates under the missing at random (MAR) assumption (Laird and Ware, 1982).

The above mentioned analyses will be performed based on a mITT principle.

2. To describe the safety and tolerability mifepristone, information on all related and unrelated SAEs will be collected. There will be accelerated safety reporting for every two adverse events in every ten participants. The specific AE(s) leading to the withdrawal of a patient from study participation will be collected, along with characteristics of the AE including severity, duration, and whether the withdrawal was at the request of the patient or was initiated by a study investigator or other clinician. The AE rate will be determined on the basis of occurrence of at least one adverse event in each participant, and the following comparisons will be carried out:
  - a. A comparison of individual adverse event rates between mifepristone and placebo.
  - b. A comparison of overall adverse event rates between mifepristone and placebo.
  - c. A comparison of severity of adverse events (grades 1, 2, 3, 4, and 5) between mifepristone and placebo
  - d. A comparison of overall adverse event rates classified as possibly or definitely attributable to study drug, between mifepristone and placebo.
  - e. A comparison of overall adverse event rates classified as possibly or definitely attributable to study drug, between mifepristone and placebo by weeks 1, 4 and 12.

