| Overall AE Grade 5                                             |                           |        |                                             |        |                                              |        |
| Overall AE not attributable to study drug                      |                           |        |                                             |        |                                              |        |
| Overall AE (possibly or definitely) attributable to study drug |                           |        |                                             |        |                                              |        |

The safety analysis will be performed based on safety population. All randomized patients who have received at least one dose of study medication will be included in the safety analysis according to the treatment groups to which they are randomized.

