#### Descriptive Outcomes:

Descriptive statistics and confidence intervals for the change from baseline to one month follow-up and to three month follow-up for each of the two treatment groups will be provided for each of the descriptive outcome measures. Additionally, comparisons between mifepristone and placebo will be performed; however, lack of statistical significance should not be construed as evidence of no clinical effect given the small sample size. All efficacy analyses on descriptive outcomes will be performed based on a mITT principle.

1. PTSD Symptom Sub-Scales
  - a. Descriptive statistics for the change in score from baseline to one month on the three PTSD symptom sub-scales (intrusions, hyperarousal, and avoidance) and confidence intervals will be provided for each treatment group.
  - b. Change in score from baseline to one month on the three PTSD symptom sub-scales (intrusions, hyperarousal, and avoidance) will be compared between mifepristone and placebo using two-sample t-test (or Wilcoxon rank-sum test if the normality assumption does not hold).
2. Depression
  - a. Descriptive statistics for the change in score from baseline to one month on the Beck Depression Inventory (BDI) and confidence intervals will be provided for each treatment group.
  - b. Change in score from baseline to one month on the Beck Depression Inventory (BDI) will be compared between mifepristone and placebo using two-sample t-test (or Wilcoxon rank-sum test if the normality assumption does not hold).
3. PTSD Symptom Severity

- a. Descriptive statistics for the change in score from baseline to one month on the PTSD Checklist (PCL) and confidence intervals will be provided for each treatment group.
- b. Change in score from baseline to one month on the PTSD Checklist (PCL) will be compared between mifepristone and placebo using two-sample t-test (or Wilcoxon rank-sum test if the normality assumption does not hold).
4. Sleep Quality
- a. Descriptive statistics for the change in score from baseline to one month on the Pittsburgh Sleep Quality Index (PSQI) and confidence intervals will be provided for each treatment group.
- b. Change in score from baseline to one month on the Pittsburgh Sleep Quality Index (PSQI) will be compared between mifepristone and placebo using two-sample t-test (or Wilcoxon rank-sum test if the normality assumption does not hold).
5. Anger

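### Two-sided 5% tests are the stated frame for comparing harms, but at about 45 per arm they detect only very large excesses, and no interval for the arm difference is stated

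*Protocol*

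**What the plan says.** Comparing drug-related adverse events between the arms is a secondary objective (Protocol 1.c.2.d), and their percentage is a secondary outcome (1.d.2, 4.k).

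The comparisons are in 4.p.1, Secondary Outcomes, item 2. It begins with "A comparison of individual adverse event rates between mifepristone and placebo" and goes on to overall rates, severity grades, events attributable to drug, and attributable events by week. Tables 4 and 5 have one rate column per arm (within each time window in Table 5), with no column for a difference, an interval or a p-value. The safety population is defined after Table 5: "All randomized patients who have received at least one dose of study medication will be included in the safety analysis".

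The inferential frame is in the closing paragraph of 4.p.1: with the primary analysis excepted, "all efficacy and safety analyses will be performed with a significance level of 5% for two-sided tests". The test for adverse events is not named. Confidence intervals appear only under Descriptive Outcomes. Those for change from baseline are within arm ("confidence intervals will be provided for each treatment group"), and item 8a gives one for plasma drug levels.

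On rash, 2.a.3 gives an expected frequency of "3.3% of persons treated at 600 mg/day", and 4.i adds: "Per the FDA's request, the investigators will explicitly inquire about the development of a rash".

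**The concern.** For the primary outcome the protocol sets hypothesis testing aside because the trial is too small for it. Section 4.n.2 says 274 to 344 participants would be needed to test a 15-point difference. The protocol then applies two-sided testing to adverse events, where differences of interest can be smaller than 15 points and event rates lower.

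A test with little power gives a non-significant result under almost any realistic excess. Without an interval for the arm difference, the reader cannot see how large an excess the data still allow. The safety data are meant to inform further studies of the drug (4.i), so what is at stake is how much reassurance is drawn from them.

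**Working it through.** **Inputs.** Sample size: "a total sample size of 90 is required, or 45 per treatment group" (4.n.2). The safety population requires one dose, so 45 per arm is the most available. Level: 5%, two-sided (4.p.1). Rash on drug: 3.3% (2.a.3). The protocol gives no placebo rash rate and no rates for other events, so those below are illustrative. Because the test is not named, both Fisher's exact test and the uncorrected chi-square test are shown.

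**The plan's own figure.** No power is stated for any harm. The stated testing sample size is 274 to 344 (one-sided 5%, 80% power, 15 points, 20% withdrawal). With n per arm = [1.645·√(2p̄q̄) + 0.842·√(p₀q₀ + p₁q₁)]² / 0.15²:
- 20% v 35%: 108.5, so 109; 109/0.8 = 136.25, so 137 per arm and 274 in total.
- 44% v 59%: 136.2, so 137; 137/0.8 = 171.25, so 172 per arm and 344 in total.

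Both agree exactly.

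**Smallest significant result with no placebo events.**
- Fisher, 6 v 0: 2·C(45,6)/C(90,6) = 2 × 8,145,060 / 622,614,630 = 0.026. For 5 v 0: 2·C(45,5)/C(90,5) = 2 × 1,221,759 / 43,949,268 = 0.056. So 6 of 45 (13%) are needed.
- Chi-square, 4 v 0: 90·(4·45)² / (45·45·4·86) = 4.19, p = 0.041. For 3 v 0: 3.10, p = 0.078. So 4 of 45 (9%) are needed. At 4 v 0 the expected count is only 2 per arm, where the chi-square approximation is poor.

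**Rash.** Expected cases on drug: 45 × 0.033 = 1.5. Chance of none: 0.967⁴⁵ = 0.22. If none is seen, the upper 95% limit (two-sided) is 1 − 0.025^(1/45) = 7.9%.

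**Power at 45 per arm.** Binomial probabilities are summed over every pair of counts at which the test rejects.

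| Placebo | Mifepristone | Fisher | Chi-square |
|---|---|---|---|
| 0% | 3.3% (rash) | 0.35% | 6.1% |
| 1% | 3.3% (rash) | 0.22% | 4.0% |
| 5% | 10% | 6% | 16% |
| 10% | 20% | 18% | 28% |
| 5% | 15% | 23% | 39% |
| 20% | 40% | 46% | 56% |
| 5% | 20% | 48% | 63% |
| 5% | 25% | 71% | 81% |
| 20% | 50% | 82% | 87% |

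The mifepristone rate needed for 80% power is 12-17% against 0%, 25-28% against 5%, 33-36% against 10% and 47-49% against 20% (chi-square to Fisher). For rash at 3.3% v 1%, the usual normal-approximation formula gives about 624 per arm.

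**What an interval would show.** Take 2 of 45 v 0 of 45; Fisher p = 0.49. The Wilson limits are 1.2% to 14.8% and 0% to 7.9%. Newcombe's interval for the difference of 4.4 points is:
- lower: 4.4 − √[(4.4 − 1.2)² + 7.9²] = −4.1
- upper: 4.4 + (14.8 − 4.4) = +14.8

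The p-value alone conveys none of this. The interval shows that an excess of up to about 15 points is not excluded.

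**The case against.** Several points stand against a harsher reading.

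- A reader might infer that harms will come out non-significant whatever the truth. The figures do not support that: 25% v 5% has 71-81% power and 50% v 20% has 82-87%.
- A reader might infer that the protocol gives no caution for harms. The sentence after the one setting the 5% level says the sample was not sized for hypothesis testing and that significance on secondary outcomes needs careful reading. Adverse events are a secondary outcome, so they are covered. The caution is general, however, and supplies no measure of uncertainty. The explicit warning that a non-significant result does not show absence of effect stands at the opening of Descriptive Outcomes and is worded for clinical effect.
- A reader might infer that every event is tested in each of three time windows. The only comparison by week listed in item 2 is (e), on overall attributable events. Table 5 shows individual events by window, but as rates.
- Section 2.a.3 says of an earlier trial of 105 v 116 patients that "there were no significant differences in the incidence of rash or multiple other potential side effects". That is background on a larger study and does not show how this trial will report its harms. The same section also gives absolute rash rates by dose.
- Intervals for adverse events are often left to the SAP, which is not at hand, and the protocol does not exclude them. Their absence alone would not be a finding. The stated choice of 5% tests as the frame for safety is.
- Item 2 opens with a descriptive aim. No decision is tied to an adverse-event p-value, and the enrolment-pause rules in 4.i use none.
- Low power for a 3.3% event is a limit of sample size. An interval adds no information, but it does display the uncertainty.

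**Conclusion.** The point holds as a mismatch between the stated frame and the sample size. Two-sided 5% tests at about 45 per arm cannot inform the adverse-event objective except for very large differences. Power is below 10% for rash at the protocol's own rate. It is about 6% to 56% for a doubling of a 5%, 10% or 20% placebo rate. It approaches or reaches 80% only for excesses of roughly 12-17 points over none, or 20-29 points over a placebo rate of 5-20%.

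These figures assume the full 45 per arm, Fisher or uncorrected chi-square tests, a placebo rash rate of 0-1%, and illustrative rates for all other events. The conclusion is the same under either test. The documents do not show that harms will be misreported or that all cautions are missing. This is an inexpensive improvement in how harms are compared and does not affect the validity of the primary analysis.

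**What to change.** In 4.p.1, Secondary Outcomes, item 2 (a-e), make the mifepristone-minus-placebo risk difference with a 95% confidence interval (score or Newcombe) the basis for comparing harms, in place of the 5% tests. Where an arm has no events, also give the exact upper limit for its rate. Add a column for the difference and its interval to Tables 4 and 5. Remove safety from the closing sentence that sets the 5% level. Extend to harms the Descriptive Outcomes warning about non-significant results.

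In descriptive items 1 to 7, where the arms are compared, give the 95% confidence interval for the between-arm difference alongside the per-arm intervals.

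The cost is wording and table shells: no new data, visits or participants. The downsides are slightly larger tables and no p-values for individual events. Name the interval method in advance, because interval and test can disagree at the margin: for 5 v 0 of 45, Newcombe gives 1.1 to 23.5 points while Fisher gives p = 0.056.
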